**[name], MD**

Department of Obstetrics and Gynecology

Table of Contents

[Abstract 5](#_Toc497206426)

[Introduction 6](#_Toc497206427)

[Literature review 7](#_Toc497206428)

[Diagnosis of preeclampsia 7](#_Toc497206429)

[Management of preeclampsia 8](#_Toc497206430)

[Administration of magnesium sulphate 9](#_Toc497206431)

[Springfusor and flow control tube 10](#_Toc497206432)

[Statement of the problem 12](#_Toc497206433)

[Justification 13](#_Toc497206434)

[Research questions 14](#_Toc497206435)

[Methods 15](#_Toc497206436)

[Setting: 15](#_Toc497206437)

[Trial design: 16](#_Toc497206438)

[Study participants: 16](#_Toc497206439)

[Intervention 16](#_Toc497206440)

[Sample size 17](#_Toc497206441)

[Randomisation 17](#_Toc497206442)

[Trial flow chart 19](#_Toc497206443)

[Study procedure 19](#_Toc497206444)

[Adverse Events Reporting 20](#_Toc497206445)

[Outcome Measures 22](#_Toc497206446)

[Data management 24](#_Toc497206447)

[Safety and monitoring 26](#_Toc497206448)

[Ethical consideration 28](#_Toc497206449)

[**Informed Consent** 29](#_Toc497206450)

[Participant confidentiality 29](#_Toc497206451)

[Benefits to participants 29](#_Toc497206452)

[References 31](#_Toc497206453)

Abbreviations

BP Blood pressure

DSMB Data safety and monitoring board

gm grams

FCT Flow control tube

HELLP Hemolysis elevated liver enzymes Low platelet

IM Intramuscular

IV Intravenous

Ml millilitres

MFM Maternal foetal medicine

MgSO4 Magnesium sulphate

PE/E Preeclampsia/Eclampsia

SAE Severe adverse events

WHO World health organisation

Operational definition

1. Acceptability of the Springfusor: assessed using a likert scale ranging from 1 very acceptable, 2 acceptable, 3 neutral 4 unacceptable and 5 very unacceptable. Participants who scored 2 or less on the Likert scale are categorized as having considered springfusor acceptable. Participants who score 3 or more are considered to have found the Springfusor device unacceptable.
2. Safety of Springfusor: During the administration of magnesium sulphate, safety of use of Springfusor will be assessed by evaluating the possible occurrence of magnesium sulphate toxicity. This will be assessed by occurrence of any of the following; respiratory depression<16/min, respiratory arrest, depressed patellar reflex, liver failure, renal failure, cardiac arrest, and need for calcium gluconate.

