# Literature review

Preeclampsia is one of the hypertensive disorders that complicates approximately 2-8% of the pregnancies [[2](#_ENREF_2)]. It is one of the leading causes of maternal and neonatal morbidity and mortality worldwide [[4](#_ENREF_4)]. Preeclampsia may affect the liver, the kidney, blood coagulation and the brain. When there is delay in control of hypertension and or termination of pregnancy, preeclampsia may progress to placental insufficiency and maternal organ dysfunction.

The risk to the fetus is due to reduced or inadequate blood supply because of the damaged placenta, where it may lead to intrauterine growth restriction and fetal demise. In addition, management of preeclampsia may require women to have an early delivery (to protect the mother or fetus from injury), which leads to premature births. Severe preeclampsia may lead to seizures (eclampsia) [[5](#_ENREF_5)]. However, women can develop eclampsia without severe disease.

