## Diagnosis of preeclampsia

Preeclampsia is a multisystem disease characterized by hypertension accompanied by proteinuria. The new onset of hypertension after 20 weeks of pregnancy (a systolic BP of >140 mmHg or a diastolic blood pressure >90 mmHg), with the new occurrence of proteinuria (>0.3g/24 hours) is the criteria for diagnosis of preeclampsia [[1](#_ENREF_1)]. Preeclampsia is usually classified as non-severe or severe [[3](#_ENREF_3)]. Progression to severe can be fast, unanticipated and fulminant. Preeclampsia is not considered severe until systolic or diastolic blood pressure exceed 160 mmHg or 110 mmHg respectively [[6](#_ENREF_6)]. The American College of Obstetricians and Gynaecologists recommend that the diagnosis of hypertension requires at least two measurements of blood pressure taken 4 hours apart, however when the blood pressures are severe, the diagnosis can be confirmed within minutes to enable timely antihypertensive therapy [[1](#_ENREF_1)]. It is also recommended that the diagnosis of proteinuria is when a 24 hour excretion equals or exceeds 300 mg/l. However, when a quick decision is require or the facility is not able to perform 24 hour protein estimation, a urine dipstick reading of 1+ is suggestive of proteinuria [[1](#_ENREF_1)].

Women with mild preeclampsia usually are asymptomatic. However those with severe preeclampsia may have headache, blurring of vision and abdominal pain (epigastric). Maternal organ dysfunction associated with severe preeclampsia may present with HELLP syndrome (hemolysis, elevated liver enzymes and low platelets), eclampsia, stroke and disseminated intravascular coagulation [[2](#_ENREF_2), [3](#_ENREF_3)]. Leeman and colleagues have indicated that the presence of the following are features of severe preeclampsia; elevated creatinine level (>1.1mg/dl), hepatic dysfunction (transaminase levels > 2 times upper limit of normal or right upper quadrant or epigastric pain, new onset of headache or visual disturbance, pulmonary oedema and or platelet count < 100x10^9^ per l [[6](#_ENREF_6)]

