## Administration of magnesium sulphate

In the management of preeclampsia and eclampsia, magnesium sulphate therapy could be given by continuous IV infusion or by administering an IV bolus and IM doses for the loading dose followed by IM injections every 4 hours. The IV regimen was described by Zuspan, whereby a loading dose of 4 gm of Magnesium sulphate IV over 10-15 minutes is followed by an infusion of 1 gm/hour continued for 24 hours after the last seizure [[12](#_ENREF_12)]. In most health facilities especially in low resource settings, the rate of infusion is controlled manually. However, in high resource settings, the IV infusion is administered by a variety of programmable electronic pumps. These electronic pumps are expensive and require electricity or battery to run it, making it less appropriate in low resource settings. In low resource settings due to unavailability of the electronic pumps, the alternative regimen described by Pritchard is used [[13](#_ENREF_13)]. The Pritchard regimen involves administration of loading dose of 4 gm of 20% magnesium sulphate IV over 10-15 minutes, immediately followed by 10 gm of 50% magnesium sulphate IM (5gm on each buttock). The maintenance dose of 5 gm of 50% magnesium sulphate IM every 4 hourly in alternate buttocks continued for 24 hours after the last convulsion or delivery of the fetus, whichever is later. The IM injections are associated with pain, hot flushes, somnolence and abscess formation at the site of injection. A number of guidelines have recommended the addition of 1 ml of lignocaine to the IM solution to alleviate the pain. Other adverse events associated with magnesium sulphate are reduced patellar reflex, respiratory depression and oliguria. The concerns about the toxicity of magnesium sulphate has been reported to result in reluctance of some of the health professionals to administer it without the availability of antidote (Calcium gluconate). However a review by Smith et al point out that the incidence of severe side effects is very low[[14](#_ENREF_14)].

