### Outcome Measures

Primary outcome:

- Acceptability of Springfusor for administration of magnesium sulphate will be assessed using a Likert scale ranging from one (very acceptable) to five (very unacceptable). The method of magnesium sulphate administration is regarded acceptable if its rated 1 and 2 on the likert scale. It is not acceptable if the ranking is three and above. Women who discontinue the method of administration by choice or due to side effects will be considered in group of unacceptable.

Secondary outcomes:

- *Rate of complications of preeclampsia and its management:* Proportion of preeclamptic women who developed magnesium sulphate toxicity, abnormal liver and renal function test as reported by the laboratory report, infection at the injection as reported by the clinician and maternal deaths
- Discontinuation: This will be assessed as study participants who do not completed doses of magnesium sulphate in 24 hour period of including the loading dose. Participants who discontinue the method of administration by choice, due to side effects or by health workers decision will be considered in group. This will be measured by the number of dose received for each arm. For the Pritchard arm (standard of care), the number of complete 6 doses equivalent to 29 gm (including loading dose) in 24 hours. In the Springfusor, the number of complete 6 doses equivalent to 24 gm (including loading dose) in 24 hours.
- *Level of pain:* The study participants will be asked to assess the severity of pain during the administration of magnesium sulphate using Visual analogue scale 1-7. The least (one) representing no pain and maximum (7) representing the worst pain imaginable.
- Safety of use of Springfusor will be assessed by evaluating the possible occurrence of magnesium sulphate toxicity. This will be assessed by occurrence of any of the following
  - respiratory depression<16/min,
  - respiratory arrest,
  - depressed patellar reflex,
  - liver failure, renal failure,
  - cardiac arrest,
  - a need for calcium gluconate.
- In addition, other side effects of magnesium sulphate like nausea, vomiting, flushing of the skin, muscle weakness, confusion and drowsiness will be noted.

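### The magnesium toxicity outcome counts liver and renal failure whatever their cause, so organ failure from preeclampsia would be scored as toxicity

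*Protocol*

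**What the plan says.** The safety outcome is defined twice, in the same terms. Under Outcome Measures: "Safety of use of Springfusor will be assessed by evaluating the possible occurrence of magnesium sulphate toxicity. This will be assessed by occurrence of any". A list completes that sentence, and one event from it suffices: respiratory depression, respiratory arrest, depressed patellar reflex, "liver failure, renal failure", cardiac arrest and need for calcium gluconate. The Operational definition section gives the same list, ending "depressed patellar reflex, liver failure, renal failure, cardiac arrest, and need for calcium gluconate". It also places the assessment within the period of magnesium administration, a limit that Outcome Measures does not repeat. Neither place asks whether the event is attributable to the drug.

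Three other passages bear on how the list should be read:

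- Literature review: "Preeclampsia may affect the liver, the kidney, blood coagulation and the brain".
- Diagnosis of preeclampsia, among the features of severe disease: "elevated creatinine level (>1.1mg/dl), hepatic dysfunction (transaminase levels > 2 times upper limit of normal".
- Administration of magnesium sulphate, after the effects of the IM injections: "Other adverse events associated with magnesium sulphate are reduced patellar reflex, respiratory depression and oliguria".

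A separate secondary outcome, complications of preeclampsia and its management, covers women who "developed magnesium sulphate toxicity, abnormal liver and renal function test as reported by the laboratory report", together with injection-site infection and maternal death.

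**The concern.** The list mixes two kinds of event. Respiratory depression or arrest, a depressed reflex, cardiac arrest and a need for calcium gluconate are signs or consequences of magnesium excess. Liver and renal failure are, on the protocol's own account, the severe end of what preeclampsia does to those organs. Because any one event suffices and no attribution is required, a woman whose liver or kidneys fail from her disease meets the toxicity outcome.

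Randomisation should balance such events between the arms, so no bias in favour of one arm is expected under the null. Two things are at stake. The toxicity rate reported for each arm would include events that magnesium did not cause. And a common background in both arms moves the risk ratio towards 1 and adds variance, which in a safety comparison errs towards finding no difference.

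**Working it through.** **1. Reading the passages together**

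| Component of the toxicity list | Among magnesium's adverse effects (Administration of magnesium sulphate)? | Organ linked to preeclampsia (Literature review; Diagnosis)? |
|---|---|---|
| Respiratory depression | Yes | Not stated |
| Depressed patellar reflex | Yes | Not stated |
| Liver failure | No | Yes, liver |
| Renal failure | No; oliguria is the nearest entry | Yes, kidney |

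Respiratory arrest, cardiac arrest and need for calcium gluconate are not in that sentence. The first is the extreme of respiratory depression, and the same section names calcium gluconate as the antidote. Liver and renal failure are the two components that the protocol's background ties to the disease rather than the drug.

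**2. The plan's own figure**

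The only sample size is for acceptability: 31% v 31% × 1.5 = 46.5%, 90% power, alpha 0.05. A two-sided, continuity-corrected calculation gives 219 per arm, and 219 × 1.10 = 240.9, so 241. The stated figures reproduce. They do not concern safety; 241 is used below only as the number per arm.

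**3. Illustration of the dilution**

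The protocol gives no rate for toxicity or organ failure, so every rate here is an assumption. Let t be the true magnesium toxicity rate in an arm and b the rate of disease-caused organ failure, equal in both arms and independent of toxicity.

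- Composite rate: q = 1 − (1 − t)(1 − b).
- Risk difference: q₂ − q₁ = (t₂ − t₁)(1 − b).
- Power: normal approximation for two proportions, two-sided 0.05, pooled variance under the null, 241 per arm.

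Example with t = 2% v 7% and b = 1%: q₁ = 1 − 0.98 × 0.99 = 2.98%; q₂ = 1 − 0.93 × 0.99 = 7.93%; ratio 7.93/2.98 = 2.7; difference 4.95 points.

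| b | Composite rates | Risk difference (points) | Risk ratio | Power |
|---|---|---|---|---|
| 0 | 2.00% v 7.00% | 5.00 | 3.5 | 76% |
| 0.5% | 2.49% v 7.47% | 4.98 | 3.0 | 71% |
| 1% | 2.98% v 7.93% | 4.95 | 2.7 | 67% |
| 3% | 4.94% v 9.79% | 4.85 | 2.0 | 53% |
| 5% | 6.90% v 11.65% | 4.75 | 1.7 | 43.5% |

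With assumed toxicity of 5% v 12% the loss is milder at low backgrounds: power 79% at b = 0, 76% at 0.5%, 74% at 1% and 58% at 5%.

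The direction does not depend on the chosen rates; the size does. The risk ratio falls quickly and the risk difference hardly moves. Power falls mainly because the variance grows.

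**The case against.** Several points limit the concern, and most of them stand.

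- **Window.** The Operational definition confines the assessment to magnesium administration, planned for 24 hours. Organ failure would have to arise within about a day to count. This favours the low end of the range, although Outcome Measures omits the limit and the disease is active in that window.
- **Severity.** The disease features listed under Diagnosis are laboratory abnormalities. Failure is a more severe and presumably rarer state.
- **Renal entry criterion.** Women with creatinine above 1.2 mg/dl are excluded, or withdrawn when the result arrives. That removes renal disease present at entry, but not later renal failure, and there is no liver equivalent.
- **Oliguria.** It is named as associated with magnesium, so a renal component is not wholly foreign to the list. Oliguria is still not renal failure.
- **Power.** The protocol sizes only acceptability and names no test for toxicity, so the power figures illustrate a test of my choosing.

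Two stronger readings are tempting and are not supported. A reader might infer harmful double counting, because the complications outcome includes "abnormal liver and renal function test as reported by the laboratory report". But that outcome also lists toxicity as a component, so the overlap is by design, and in a proportion of women each woman counts once. A reader might also infer that the emergency safety trigger is compromised. It is not: the 12.5% threshold under Stopping rules uses only respiratory depression due to magnesium toxicity.

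The investigator's causality review under Management of adverse events does not answer the point. It covers serious adverse events in relation to the device and does not feed the outcome definition.

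**Conclusion.** The concern holds as a definitional fault in a secondary safety outcome. Followed as written, the protocol would score disease-caused liver or renal failure as magnesium toxicity, which inflates the toxicity rate and pulls the risk ratio towards 1. It is not a matter left to an analysis plan, since the protocol fixes the list in two places.

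The size cannot be determined from the document. The window, the severity implied by failure and the creatinine criterion point to a low background. On the assumed 2% v 7%, a background of 0.5% to 1% costs 5 to 9 percentage points of power (76% to 71% or 67%); 3% or more would be needed for a large loss. These figures assume equal background in both arms and independence from toxicity. The documents do not support saying that real harm would be hidden. This is a cheap improvement, to be considered.

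**What to change.** In the Operational definition and in Outcome Measures, restrict the toxicity outcome to the magnesium-related signs already listed: respiratory depression or arrest, depressed patellar reflex, cardiac arrest and need for calcium gluconate. Report liver and renal failure under the complications outcome, beside the liver and renal function tests. Keep the present broad list as a supportive analysis. Use the same time window in both places.

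The cost is a rewording of one definition in two places. Each component is already named as an outcome, so no new data are needed. The downside is fewer events in the toxicity outcome.

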### Data management

**Data handling**

Case record forms will be provided for each participant. Participants will be identified by their study identification number on the case record form. Participant names will not be entered into the computerized database. All participant record forms will be kept in individual files in a secure filing cabinet. Only authorized study personnel will have access to these files. The case record forms will be cross checked by the PI and study coordinator. All corrections will be made on case record forms by striking through the incorrect entry with a single line and entering the correct information adjacent to it. The correction will be initialed and dated by the investigator.

Data will be transferred from the case record forms into a computerized database (Epi data version 3.1) by data entry personnel and will be doubly entered to verify accuracy of entry. For quality control, check programs will be written into the database to limit the entry of incorrect data and ensure entry of data into required fields.

**Data quality assurance**

A pilot study of 5 study participants on the use of Springfusor for the administration of magnesium sulphate will be done prior to implementation of the trial to get familiar with the device and test the study instruments. All members of the study team will be trained in the study protocol prior at the onset of the trial. The research assistants will complete case record forms. These forms will be reviewed by the study coordinator and PI for completeness and accuracy. Study group meetings will be conducted by the PI to assess progress of the study, address any difficulties, and provide performance feedback to the members of the study group. The study site will be open to review by the IRBs and or to inspection by appropriate regulatory authorities.

**Data analysis**

Data analysis will be performed by the PI. Descriptive statistics will be used to summarize baseline characteristics of study participants and assess if randomization was successful. The baseline characteristics will too give guidance as to which variables need to be adjusted for in the final analysis.

Acceptability and safety data will be evaluated using intention-to-treat (ITT) analysis. For comparing the maternal health outcome between intervention and control arms, the main analyses will look at the following variables;

1. Proportion of study participants who regarded magnesium sulphate administration using Springfusor or Pritchard route was acceptable. This will be compared using chi-square.
2. *Rate of complications of preeclampsia and its management:* Proportion of preeclamptic and eclamptic women who developed magnesium sulphate toxicity, abnormal liver and renal function test, infection at the injection and maternal deaths
3. The intensity of pain will be analysed using a ttest and presented as means and standard deviation
4. *Feasibility of Springfusor pump use:* The proportion of women who have a Springfusor used for the administration of magnesium sulphate and experience some technical problem with its use, blockage of FCT, the number of attempts made prior to successful Springfusor placement, the number of failed Springfusor placement and the number of FCTs used and spilled magnesium sulphate.
5. *The reliability of the springfusor:* The intra-class correlation coefficient (ICC) will be calculated. The closer the ICC to 1, the higher the reliability, ICC <0.4; the poor the reliability and ICC 0.4-0.75; the fair the reliability.

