# Abstract

**Introduction:** Magnesium Sulphate is the drug of choice for prevention and treatment of seizures in preeclampsia and eclampsia. It is administered parenterally by intravenous (IV) and or intramuscular (IM) routes. The IM regimen used in low resource settings, requires repeated painful injections which may be a barrier to optimal utilization whereby, there is frequent omission of some doses or increased interval between maintenance doses and low patient acceptability of magnesium. In addition, the IM regimen may potentially lead to abscess formation. There is a need to test an alternative way of providing Magnesium Sulphate that avoids the adverse events of IM regimens.

**Objective:** To assess the acceptability and safety of Springfusor device in the administration of magnesium sulphate in preeclampsia and eclampsia.

**Methods:** The study will be open label clinical randomized trail conducted at Mulago national referral and teaching hospital, where, 482 women diagnosed with preeclampsia and eclampsia will be randomized in blocks to either Springfusor device or standard of care for the administration of magnesium sulphate. Women in the Springfusor group will have their loading dose (4 gm of 50% Magnesium sulphate in 10 ml syringe administered over 20 minutes) and maintenance therapy (4 gm of 50% Magnesium sulphate in 10 ml syringe administered over 4 hours. The 4 gm maintenance dose will be repeated every 4 hours for 24 hours) of Magnesium sulphate through an IV infusion administered using a Springfusor pump. The control group will have Magnesium sulphate administered according to the Pritchard regimen (standard hospital practice). The Pritchard regimen involves administration of loading dose of 4 gm of 20% Magnesium sulphate IV over 15-20 minutes, immediately followed by 10 gm of 50% Magnesium sulphate IM (5gm on each buttock). The maintenance dose of 5 gm of 50% Magnesium sulphate IM every 4 hourly in alternate buttocks continued for 24 hours.

The primary outcome is the acceptability of administration of Magnesium sulphate using Springfusor assessed using a Likert scale. The other outcomes are discontinuation and complications in the two arms. Analysis will be intention to treat.

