- *Feasibility of Springfusor pump use: ⃰* The proportion of women who have a Springfusor used for administration of magnesium sulphate and experience some technical problem with its use, blockage of FCT, the number of attempts made prior to successful Springfusor placement, the number of failed Springfusor placement and the number of FCTs and spilled magnesium sulphate used will also be documented.
- The *reliability** of the Springfusor to administer magnesium sulphate in the prescribed time will assessed for the loading period and the maintenance period. The intra-correlation coefficient for the device will be calculated.

These outcomes will be compared between the women in the two arms. A *outcome will be reported only for women who will have magnesium sulphate administered using Springfusor

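### Intention to treat is the only population named for safety, so by-arm rates can misstate harm among women actually treated with the pump, in a direction and by an amount the protocol leaves unknown

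*Protocol*

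**What the plan says.** The Abstract states the aim as "To assess the acceptability and safety of Springfusor device in the administration of magnesium sulphate in preeclampsia and eclampsia" and adds "Analysis will be intention to treat". The Data analysis section applies this to safety by name: "Acceptability and safety data will be evaluated using intention-to-treat (ITT) analysis".

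Outcome Measures words the safety outcome as a question about the device: "Safety of use of Springfusor will be assessed by evaluating the possible occurrence of magnesium sulphate toxicity". The same section expects incomplete pump treatment. On discontinuation it says "Participants who discontinue the method of administration by choice, due to side effects or by health workers decision will be considered in group". Under feasibility it will record "the number of attempts made prior to successful Springfusor placement, the number of failed Springfusor placement".

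Only the starred outcomes, feasibility and reliability, are limited to women who actually had the device: such an "outcome will be reported only for women who will have magnesium sulphate administered using Springfusor". Toxicity, complications and side effects carry no star.

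**The concern.** Intention to treat compares the two strategies as assigned. That suits acceptability, and it is also a valid randomised comparison of complications. It does not by itself answer whether magnesium sulphate given through the pump is safe, because the Springfusor arm may include women who had little or no pump treatment. Their events, or absence of events, enter the pump arm's rate with no record in the analysis of which method was in use.

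The Justification and Benefits sections say the results may be used to argue for scale-up if the device is advantageous. A reader of that argument will want the harm rate among women who were on the pump. The protocol already accepts this principle for feasibility and reliability, but not for toxicity.

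**Working it through.** **Inputs from the protocol**
- Women per arm: 241 (Sample size; 219 × 1.10 = 240.9).
- Drug over 24 hours: 28 g in the pump arm and 39 g in the control arm (Intervention). The discontinuation definition uses other totals, 24 g and 29 g, but the control is again the higher.
- Emergency DSMB trigger: respiratory depression above 12.5%, counted in the Springfusor arm (Stopping rules).
- Rates of leaving the pump, of failed placement and of toxicity by route: none given.
- Treatment after leaving or failing to start the pump: not stated.

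The protocol has no figure of its own to reproduce on this point. What follows shows how the mechanism works and does not estimate its size.

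**Formula.** Let f be the share of the Springfusor arm not treated by pump at all, p the harm rate among pump users, and q the rate among the others. The by-arm rate is (1 − f)p + fq. If the others receive the control regimen and so have the control rate q, the difference between arms is (1 − f)(p − q).

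**Case A: more harm on the pump** (assumed p = 12.5%, q = 5%; true difference +7.5 points). Power is the two-sided 5% normal approximation with 241 per arm; with no dilution it is 83%.

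| f | Women | Arm rate | Difference | Power |
|---|---|---|---|---|
| 10% | 24 | 11.75% | +6.75 | 76% |
| 20% | 48 | 11.0% | +6.0 | 68% |
| 30% | 72 | 10.25% | +5.25 | 58% |

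**Case B: less harm on the pump** (rates reversed: p = 5%, q = 12.5%; true difference −7.5 points). At f = 10%, 20% and 30% the arm rates are 0.9 × 5 + 0.1 × 12.5 = 5.75%, 0.8 × 5 + 0.2 × 12.5 = 6.5%, and 0.7 × 5 + 0.3 × 12.5 = 7.25%. The differences are −6.75, −6.0 and −5.25 points. Here the by-arm rate makes the pump look worse than it is among its users.

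**Case C: no further drug and no events among the others** (p = 12.5%, q = 0 in that group). At f = 20% the arm rate is 0.8 × 12.5 = 10.0%. Harm is understated with no crossover at all.

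**The 12.5% trigger.** The rate among users at which the arm reaches the trigger is (12.5 − fq)/(1 − f). With f = 20% this is 12.5/0.8 = 15.6% for q = 0, and (12.5 − 1.0)/0.8 = 14.4% for q = 5%. If q exceeds 12.5%, the trigger is reached at a rate among users below 12.5%.

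**Limit of the formula.** It treats the share f as never exposed to the pump. A woman who has toxicity on the pump and stops because of it is counted in the Springfusor arm as she should be. Her event is not diluted.

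**The case against.** A reader might infer that women who leave or never start the pump move to intramuscular treatment, so that any pump harm is diluted and the plan leans towards declaring the pump safe. The documents do not support this, for four reasons.

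- No section says that these women receive the intramuscular regimen. Discontinuation is defined as not completing the doses, which fits no further drug equally well. "the number of failed Springfusor placement" may count failed attempts rather than women who never start.
- Dilution requires less harm off the pump than on it. The control regimen gives more drug. The protocol attributes this to assumed lower bioavailability of the intramuscular route, which leaves open which route is more toxic. Injection-site infection after a switch would count against the pump.
- Harm on the pump before stopping still counts in the arm.
- The protocol makes no claim that the pump is merely no worse. It hopes for fewer side effects, and against that hope a shift towards no difference is conservative.

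All four stand. Two further objections stand in part. Management of adverse events has the PI judge each serious event's relation to the device, and Safety and monitoring sends serious events to the DSMB. So the by-arm comparison is not the only safety review, but neither channel gives rates of toxicity or side effects by method received. It can also be said that a supplementary safety set is commonly left to a statistical analysis plan, and that the protocol does not say it will use intention to treat alone. That would answer a silent protocol. This one names a safety population, and names one that does not fully match its device question.

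**Conclusion.** The point holds in a limited form. Intention to treat is a proper comparison of the two strategies and is not an error. What the protocol lacks is an accompanying safety summary by method actually received, although its safety outcome concerns use of the device and it expects incomplete pump treatment.

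The by-arm rate can misstate harm among pump users in either direction. The size cannot be derived. In the illustrations, the difference between arms shrinks in proportion to the share never treated by pump, so by 20% if that share is 20%. This rests on assumed harm rates and on those women having the control arm's rate. If few women leave early or fail to start, the effect is negligible. Certain dilution, or a bias in the pump's favour, is not established.

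This is a cheap improvement, not a defect that undermines the trial.

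**What to change.** In the Data analysis section:

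1. Keep the intention-to-treat comparison for acceptability and for safety.
2. Add a supplementary safety table of all women who received any magnesium sulphate, grouped by method actually received: pump only, intramuscular regimen only, or both.
3. Assign acute events (respiratory depression, loss of reflexes, side effects) to the method in use at onset.
4. Report delayed events (site infection, liver or renal abnormality) by all methods received before onset. Otherwise an event caused on the first method but appearing after a switch would be charged to the second.
5. State that this table is not protected by randomisation. Women who leave because of side effects are a selected group.
6. If the two tables differ, do not base a conclusion on device safety on the intention-to-treat table alone.

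The cost is a short paragraph and one case record form field for the method in use at onset. The monitoring in the Study procedure section (every 5 minutes during loading, hourly during maintenance, four-hourly for side effects) should already give the timing of acute events. The downside is a second, non-randomised comparison that must be read with care.
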